### 3.2.2 Population

Inclusion criteria:

- HIV-positive adolescents and adults (> 14 years of age)
- Not acutely ill
- For CAGs, UAGs, and Fast-Track models: on ART for at least 6 months
- For the START model: ART naïve and meet the Zambian HIV guidelines for treatment initiation

Exclusion criteria:

- For CAGs, UAGs, and Fast-Track: CD4 < 200 in the last 6 months
- For CAGs, UAGs: Inability to participate in the group activities due to cognition deficits or mental illness.
- Unable to provide consent or unwilling to participate in study
- Pregnancy

###

### 3.2.3 Procedures

1. *Description of Interventions:*

*CAG:* Both rural and urban sites will be eligible for the CAG intervention, consisting of facilitated groups of six people based on geographic proximity of home address and patient preference. This group of six people, will meet monthly at a designated place in the community to provide support and receive medications. Each month one of the members will rotate visiting the clinic for their routine medical visit and will pick up medications for the entire CAG and bring them back to the community. This rotation schedule will recur every six months. The CAG will have a self-selected CAG *leader* within their group to serve as the primary point of contact for the group. They will receive additional support from a facility lay HCW termed a CAG *supervisor.* Patients may be referred to the facility (“up-referred”) for care based on presence of symptoms (acute illness) or patient preference. If up-referred for acute illness, patients will be eligible to continue receiving their ART and adherence support through their CAG while receiving additional clinical care at the facility.

*UAG:* Urban sites will be eligible for the UAG model in which patients will be joined into a UAG group consisting of 30 people. Each UAG group will meet every two to three months at a designated site (either at the clinic facility or another site in the community). Patients will receive (a) group adherence counseling led by a lay HCW (b) two to three month supply of ART medications via a pharmacy tech (c) attendance record and symptom assessment. As in the CAG model, patients may be up-referred for care based on acute illness or patient preference. Patients will continue to visit the facility for a routine medical visit with a professional HCW every six months.

*FAST-TRACK:* Urban sites will also be eligible for the FAST-TRACK intervention. The FAST-TRACK model will provide low-cost additional space (e.g. a mobile unit placed at clinic facility) that will be staffed by a pharmacy technician (to dispense drugs) and two lay health care workers (to provide brief symptom screening to identify patients in need of higher-level care). Patients will be required to visit the FAST-TRACK center every two to three months and will receive ART supply. Data will be captured using the national HIV SmartCare e-card system. Patients will continue to visit the facility for a routine medical visit with a professional HCW every six months.

*START:* Both rural and urban sites will be eligible for the streamlined ART intervention that enables more rapid initiation of ART in order to decrease loss before treatment. Current (2014) Zambian national care and treatment guidelines recommend three structured treatment preparation sessions prior to the initiation of ART for HIV positive non-pregnant adults, adolescents and children. This process can take between 2-4 weeks to complete after determination of ART eligibility. The START model aims to deliver a higher intensity of treatment services by offering same-day CD4 testing and results, streamlined adherence counseling, and quicker initiation of life-long ART to patients enrolling in HIV care and treatment services.

1. *Patient recruitment:*

*At all intervention sites:* The facility staff will identify eligible patients during routine clinic visits and notify the study research assistant about the potential study participant. The research study assistant will assess patient willingness to participate in the intervention and will obtain informed consent for study participation.

For the START model: ART eligibility will be determined by facility staff using national guidelines (excluding pregnant women as they are routinely routed through ANC) and expedited by the provision of on-site CD4 testing using point of care platform after enrollment into the study, for all new HIV infected patients at the facility, and for all returning facility patients that are pre-ART and due for routine CD4 monitoring to determine their eligibility status. Eligible participants will be enrolled into this intervention after they provide informed consent for study participation. No active follow up of participants will be done, after the participant completes the initiation of ART process, during the 12-month follow-up period. At study exit, participants will receive a viral load test as explained below.

*At control sites:* As a cluster randomized study approach is being implemented for CAG and UAG, eligible patients at control sites will be approached for willingness to participate in the intervention. Those who are willing will be enrolled in the study and consent will be obtained to use patient data within SmartCare to evaluate the primary outcome of retention. A viral load measurement will be obtained at baseline and at the end of the follow-up period. No further actions will occur among control site participants and all other study procedures refer only to intervention site participants.

1. *Baseline viral load testing*

For participants enrolled into the CAG and UAG intervention and control groups and into the Fast-Track intervention, dry blood spot specimens will be obtained via a finger prick from each participant for baseline viral load testing after completion of the intake and informed consent process.

At CAG and UAG sites, specimens will be stored and analyzed at the end of the follow-up period. Routine viral load testing, conducted as part of standard clinical care according to national ART treatment guidelines, will be promoted at these sites.

At Fast -Track sites, specimens will be transmitted to the CIDRZ central laboratory for testing and results will be communicated to clinics (using current standard procedures for laboratory results reporting) and to study staff.

Patients who are found to not be virologically suppressed (defined as viral load > 1,000 copies/mL) will remain eligible to continue to participate in the Fast-Track model though they will be scheduled for additional visits to the clinic based on national ART treatment guidelines as well as receive intensified support from the lay HCW.

1. *Baseline CD4 testing*

For intervention participants enrolled into the CAG, UAG and Fast-Track models, study staff will liaise with the clinic to facilitate baseline CD4 testing after completion of the intake and informed consent process.

Specimens will be transmitted to the CIDRZ central laboratory for testing and results will be communicated directly to clinics (using current standard procedures for laboratory results reporting) and to study staff. Patients with CD4 count <200 will remain eligible to continue to participate in the models but may receive additional visits to the clinic at the discretion of the provider according to current standard of care.

1. *Costing*

Information will be collected during the intervention period on a subset of participants in each model using a semi-structured questionnaire to assess direct and indirect health costs of the intervention. Administrative data, where needed, will also be used.

1. *Exit viral load testing and patient exit-survey*

In all four models, patients will have an exit viral load test performed at the end of the 12-month intervention period. In CAG, UAG, and Fast-Track models, participants will be administered a patient exit-survey to assess patient satisfaction and patient centeredness.

A summary of the routine schedule of activities within four models of differentiated care is shown in Appendix 5.

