## 3.2 Objective 2: To evaluate the effectiveness, efficiency, and health care quality of a differentiated system of care that includes targeted models of care.

Overall, this objective seeks to evaluate the effectiveness of a differentiated system of HIV care delivery in which the frequency, type, or intensity of contact with the health system is tailored to patient needs. The differentiated system of care includes targeted evaluation of three care models targeting patients stable on ART [community adherence groups (CAGs)], urban adherence groups (UAGs), and fast-track clinic visits), complemented by a model designed for HIV infected patients not yet on therapy (streamlined ART initiation (START)). An overview of these models is available in Appendix 4. These models will be implemented simultaneously, and will be evaluated using a common evaluation framework that includes effectiveness (with a primary outcome of retention), efficiency, and quality.

Patients who meet eligibility criteria, express willingness to participate, and provide written informed consent at the selected intervention sites will be enrolled. Interventions will be targeted by the type of site (rural/urban, high/low volume), baseline retention at site, and by patient status (treatment naïve vs experienced, stability on treatment).

### 3.2.1 Methodology for Objective 2

To evaluate the effectiveness, efficiency and quality of the differentiated care models, a matched cluster randomized design approach is proposed for the CAG and the UAG models, due to substantial weaknesses in existing regional observational pilot data in various settings. Cluster level analysis is being pursued as introduction of the intervention occurs at the clinic level. Randomization is being proposed to account for selection bias encountered in previous observational analyses. As there is little to no observational or implementation data for the Fast-Track and START models, and the goal is to generate such data in Zambia, a difference-in-difference design will be used to calculate the effect of the models on the outcomes of interest.

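### CAG and UAG recruitment is written separately for intervention and control clinics, apparently with allocation known, so differential enrolment can bias the unadjusted primary comparison

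*Protocol*

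**What the plan says.** Protocol 3.2.1 gives the reason for randomising clinics in the CAG and UAG comparisons: "Randomization is being proposed to account for selection bias encountered in previous observational analyses".

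Protocol 3.2.3 then describes patient recruitment under two site headings.

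- **Intervention sites.** "The facility staff will identify eligible patients during routine clinic visits and notify the study research assistant about the potential study participant". Next, "The research study assistant will assess patient willingness to participate in the intervention and will obtain informed consent for study participation".
- **Control sites.** "eligible patients at control sites will be approached for willingness to participate in the intervention. Those who are willing will be enrolled in the study". Their consent covers use of SmartCare data, and viral load is measured at baseline and at the end. The text does not say who identifies or approaches these patients, or in what order.

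Three other places bear on the point.

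- Section 1.6 promises a systematic offer up to the enrolment cap. It says this of eligible patients at the intervention clinic and has no matching statement for control clinics.
- Section 3.2.3 forms CAGs as "facilitated groups of six people based on geographic proximity of home address and patient preference". Nothing equivalent is asked of control patients.
- Section 3.2.5 makes Kaplan-Meier estimates and log-rank tests by intervention condition the CAG/UAG analysis. Adjustment for baseline patient characteristics is a secondary analysis.

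**The concern.** Randomising clinics balances the clinics' eligible populations in expectation. It does not balance the patients analysed if these enter one at a time, after allocation, by a route that depends on the arm.

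The eligibility criteria in 3.2.2 leave room for this. They set no requirement on past attendance, so earlier lateness, a plausible predictor of a pick-up more than 7 days late, can vary freely among eligible patients. Some criteria, such as acute illness and ability to take part in group activities, call for judgement. Enrolment stops at a cap, so at a busy clinic not every eligible patient need be offered a place.

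If the arms enrol patients with different underlying risk, the log-rank comparison mixes that difference with the effect of the model. Matching clinics does not remove a difference that runs the same way in every pair, and more patients per site do not remove it either. It would be a form of the selection bias that 3.2.1 says randomisation is there to address.

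**Working it through.** **1. The two recruitment routes side by side (3.2.3 and 1.6)**

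| Step | Intervention clinics | Control clinics |
|---|---|---|
| Who identifies patients | Facility staff, at routine visits | Not stated |
| Who assesses willingness and takes consent | Research assistant | Not stated |
| What willingness means | Joining a group that will run | Joining one not provided during the study |
| Order of approach | Systematic up to the cap, not defined further | Not stated |
| Group formation (CAG) | Home proximity and preference | None |

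The eligibility criteria are common to both. No step provides for listing patients before allocation is disclosed, for recruiters unaware of allocation, or for one shared procedure.

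**2. The plan's own power figure**

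The inputs are the Appendix 6 base row: pi0 = 0.6, pi1 = 0.3, k = 0.1, j = 30, n = 5, alpha = 0.05 (taken as two-sided). The matched-pair cluster formula is

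power = Phi( sqrt[ (n − 2)(pi0 − pi1)² / V ] − 1.96 ), with V = [pi0(1 − pi0) + pi1(1 − pi1)]/j + k²(pi0² + pi1²).

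- V = (0.24 + 0.21)/30 + 0.01 × (0.36 + 0.09) = 0.0150 + 0.0045 = 0.0195.
- (n − 2)(pi0 − pi1)²/V = 3 × 0.09/0.0195 = 13.85, with square root 3.72.
- Power = Phi(3.72 − 1.96) = 0.961, against 0.96 stated.

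The figure reproduces. Differential recruitment does not change it, because the problem is bias and not precision.

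**3. What a case-mix difference would do**

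Inputs from 3.2.5: 5 pairs, 120 patients per site, k = 0.10, control risk 0.65. The assumption is no true effect, with intervention enrollees at risk 0.65 − d. Cluster risks were drawn from a normal distribution with standard deviation k times the risk, and outcomes were binomial. Each trial was tested with a two-sided paired t-test on the five cluster differences, over 20,000 runs. The formula in step 2 serves as a check. For d = 0.05:

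- V = (0.2275 + 0.2400)/120 + 0.01 × (0.4225 + 0.3600) = 0.01172.
- sqrt(3 × 0.0025/0.01172) = 0.80.
- Phi(0.80 − 1.96) = 0.123.

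| Assumed d (points) | Significant, simulation | Significant, formula |
|---|---|---|
| 0 | 5.2% | – |
| 2 | 6.1% | 5.0% |
| 5 | 12.7% | 12.3% |
| 10 | 37.5% | 37.3% |
| 15 | 67.7% | 70.9% |

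The planned effect is 50% of 65, or 32.5 points. A 10-point difference is 10/32.5, about a third of it. A paired cluster test was used, not the planned log-rank test, so that the rise reflects case mix alone.

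**4. How such a difference could arise (assumptions only)**

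- If a share f of intervention places goes to patients with risk r, the shift is f × (0.65 − r). With f = 0.2 and r = 0.45 it is 4 points; with f = 0.4 and r = 0.45, 8 points; with f = 0.4 and r = 0.35, 12 points.
- Suppose instead that 20–30% of eligible patients are poor attenders with risk 0.85–0.90, and that intervention sites enrol them at 75% down to 0% of the control rate. The shift is then about 1 to 11 points. For example, 30% at risk 0.90 leaves the others at (0.65 − 0.27)/0.70 = 0.543. Half-rate enrolment makes poor attenders 0.15/0.85 = 17.6% of enrollees, with overall risk 0.606, a shift of 4.4 points.

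None of these shares or risks is in the protocol. If intervention clinics over-enrolled poor attenders, the sign would reverse.

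**The case against.** The strongest reply is that the protocol already addresses the selection bias it criticises. Its literature review faults earlier CAG work for having no comparable stable patients outside the groups. Control patients here meet the same criteria and say that they would join, so joiners are compared with would-be joiners. That is a real safeguard and should be credited. It does not govern whom staff put forward, and willingness is real in one arm and hypothetical in the other.

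The systematic offer in 1.6 applies where a motive to choose among patients would most plausibly lie. That also counts, but the offer is not defined and does not extend to control clinics.

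Three limits on the criticism stand in full.

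- A reader might infer that facility staff choose and also consent the patients. At intervention sites they identify and notify; the research assistant takes consent.
- A reader might infer that the clinics are already delivering the models when they recruit. Section 3.2.6 places enrolment in Months 10–15 and implementation in Months 16–27, and no randomisation date is given. That allocation is known at consent is an inference from recruitment being written by site role, and from 3.2: "Patients who meet eligibility criteria, express willingness to participate, and provide written informed consent at the selected intervention sites will be enrolled".
- The control route is under-specified as much as it is shown to differ.

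Some detection is planned: baseline viral load in both arms, record data for all patients, a baseline-adjusted secondary analysis, and a fidelity measure that needs the number of identified and eligible patients for the models. Balance tables and covariate details may properly sit in an SAP. Who identifies and approaches patients is trial conduct. The protocol fixes it by arm, and no later analysis can undo selection on unmeasured factors.

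**Conclusion.** The concern holds as a risk of bias. Recruitment to the CAG and UAG comparisons is written by arm, apparently with allocation known, without a common identification route, and the primary comparison is unadjusted. Following the plan as written can therefore reintroduce selection bias.

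A reader might go further and infer that the comparison is confounded in favour of the models because intervention staff will refer reliable attenders. The documents do not support that. They say nothing of staff preference, and since the models are meant to relieve travel burden and congestion, patients who struggle to attend could equally be drawn to them. Nor can a shift of 4–12 points be read as an estimate; it follows from assumed shares and risks, with no selection in the control arm.

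The size is known only conditionally. With 5 pairs, 120 per site, k = 0.10, control risk 0.65 and no true effect, a 5-point case-mix difference would raise false positives from about 5% to about 13%, and a 10-point difference to about 38%. The 65% is itself the protocol's figure for the first year after starting ART, whereas the patients enrolled have been on ART for at least 6 months.

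**What to change.** In 3.2.3, state one procedure for all CAG and UAG clinics in both arms:

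- Generate from SmartCare the list of patients who meet the record-based criteria of 3.2.2, before allocation is disclosed to the clinic where that is still possible. Criteria that need judgement are checked at the visit.
- Approach every listed patient consecutively as they attend, until the cap is reached.
- Use the same research-assistant role and the same willingness script in both arms. For CAG, include willingness to join a group from the patient's own area.
- Keep the same log of approached, ineligible and refused patients.
- Compare prior pick-up lateness of listed and enrolled patients by arm, over the ART history available (at least 6 months).

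In 3.2.5, make the analysis adjusted for prior pick-up lateness the primary CAG/UAG analysis, with the unadjusted log-rank test as supporting.

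Consecutive approach is preferable to a strict random order, which fits poorly with forming groups of six neighbours and with patients arriving on their own schedule. If allocation is already known at a clinic, the list, common script and log still limit discretion.

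The cost is slightly slower enrolment and group formation and a little more data work; no extra patients are needed. Real and hypothetical willingness will still differ somewhat. The log makes that visible but does not remove it.

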### 3.2.4 Measurements

We will use information from routine clinical documentation, which includes:

1. Socio-demographic, laboratory, clinical, and pharmacy data

We will extract standard de-identified socio-demographic, laboratory and clinical data for all patients (intervention and control) from the patient’s electronic medical records.

1. Participant attendance, individual ART pick-up, and symptom assessment for UAG, CAG, and Fast-Track

We will use model specific registers that include information such as 1) Attendance, 2) Receipt of medications 3) Symptom checklist 4) Whether patient prefers to remain in care model or return to standard clinical care. This information will be entered into the study database using a tablet.

In addition, the study will also measure additional processes and outcomes related to each of the four models of care, which includes:

1. Movement between tiers for UAG, CAG and Fast-Track

The presence of symptoms or a patient’s desire to return to standard care will trigger an up-referral to the facility. Patients with acute illness, once stabilized, will be down-referred back to the model. Movement between tiers will be measured using a register that will document any up-referral after initial study enrollment. This information will be entered into the study database using a tablet. Down-referrals will be captured by measuring assigned frequency of clinic visit in the electronic medical record.

1. Patient satisfaction and patient-centeredness for UAG, CAG and Fast-Track

Patient satisfaction and centeredness will be measured as part of a semi-structured patient-exit survey that will be conducted after the 12-month intervention period.

1. Viral load testing

Viral load testing (at baseline and exit) using dried blood spot specimens will be conducted as noted in the procedures section.

1. Costing

A semi-structured costing questionnaire will be administered to a subset of intervention participants to assess direct and indirect health costs of the intervention (as noted in the procedures section). In addition, to calculate the resource use of each activity, we will use time-in-motion studies among patients and health care workers prior to and during the intervention.

1. Process data will be collected through qualitative assessments (i.e. HCW interviews during and at the end of follow-up period) and facility-level assessments (i.e. frequency of pharmacy stock outs).

### 3.2.5 Analytic Approach and Sample Size Considerations

*a. Outcomes and Analysis*

The primary outcome in three models that target retention in care (CAG, UAG, Fast-track) is defined as time to first missed pharmacy pick-up (> 7 days late). For the START model which targets ART initiation, we use the date of ART initiation as the primary outcome. To evaluate the impact of CAG and UAG interventions, we will use Kaplan-Meier estimates of time to the primary outcome, stratified by intervention condition, using log rank tests. For Fast-track and START, our primary analysis will take a difference-in-difference approach in which we estimate the difference in the change in the rate of the outcome between intervention and control settings. In secondary analyses of the primary outcome, we will explore longer intervals of lateness that comprise a missed pharmacy visit (14 and 30 days) as well as adjustment for baseline patient characteristics. We will also explore analysis using medication possession ratio (MPR) as the outcome and other metrics of retention ^17^ that incorporate both frequency of missed visit as well as interval of time before return.

The secondary outcomes will focus on implementation and quality (see Appendix 2).

a. *Implementation Outcomes*

- *Feasibility* will be evaluated qualitatively through analysis of interviews and focus groups.
- *Costs* will be evaluated quantitatively using “bottom-up” activity-based micro-costing techniques (see Measurements section above) and “top-down” evaluation of budgets and spending reports, based on calculations of DALY’s.
- *Fidelity* of the intervention models will be assessed through estimates of the proportion of identified and eligible patients successfully enrolled in a model, the proportion of missed visits, and the proportion of CAG/UAG still functioning at the end of the 12-month intervention period.

*b. Quality Outcomes*

We use the framework offered by the Institute of Medicine to define quality outcomes.:

- *Access* will be evaluated using time (days) from positive symptom screen to appropriate referral.
- *Efficiency* will be assessed using cost-effectiveness analysis. We will consider the incremental cost per additional patient retained and the cost per death averted using effectiveness data from each model.
- *Safety* will be evaluated by estimates of the proportion of patients with appropriate laboratory monitoring and symptom screening.
- *Equity* will be assessed by comparing retention rates between adults and adolescents and men and women.
- *Patient-centeredness* will be assessed through comparison of means in the results of appropriate dimensions in the semi-structured patient exit-survey.

*c. Patient Outcomes*

- HIV RNA: we compare the proportion of patients suppressed at one year among those exposed to the intervention and control conditions using mixed effects logistic regression
- Satisfaction: we will compare the effect of the intervention on patient satisfaction through mixed effects linear regression.

1. *Sample Size Considerations*

- CAG/UAG: Existing program data suggest that 65% of patients are at least 7 days late for a pharmacy refill visit during their first year in HIV care after starting ART and that 95% of clinics fall within 15% (that is 50 to 80) of this estimate. Thus, a conservative matched co-efficient of variation is estimated to be 0.10. We assume a 50% reduction in missed pharmacy visits due to CAG and UAG. Under these assumptions, for the CAG intervention, our selection of five clinics and 120 patients per site (in 20 CAGs per site assuming complete enrollment), the study will be powered at 96%. Under more conservative assumptions about between clinic variability and the effect size (Appendix 6) this sample size yields power of over 80%. For the UAG intervention, our target sample size is 4 UAGs at each of the five intervention sites with 30 people in each UAG and therefore 120 participants per site (total of 600 participants across sites). Under the same assumptions about coefficient of variation and the effect size as for the CAG model, this sample size yields power of > 90% and is robust to varying assumptions about correlation (See Appendix 6).
- Fast-track: Our target sample size for Fast-track is 200 patients at each of four sites (two intervention sites and two control sites; n=800 total). Assuming baseline 80% of patients miss a pharmacy visit in a year of care, which we anticipate will fall to 40%, we have 80% power.
- START: Assuming ART initiation at 2 weeks rises from 60% to 85%, 100 patients at each of eight sites (four intervention and four control sites; n=800 total), rho of 0.15 yields an anticipated power of 78%. No more than 200 patients will be enrolled into the study to receive POC CD4 testing with their consent. Enrolment will stop when we reach 100 patients who are eligible for ART initiation.

No control patients will be actively enrolled in START and Fast Track sites. We will use routinely collected, de-identified, aggregated data to evaluate the primary outcome of retention (Fast Track) and days to ART initiation (START).

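### The primary CAG/UAG test is an ordinary log-rank by arm in a matched cluster-randomised design; on the protocol's planning values its false-positive rate is near 30%, not 5%

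*Protocol*

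**What the plan says.** Section 3.2.1 sets the design: "a matched cluster randomized design approach is proposed for the CAG and the UAG models". It adds: "Cluster level analysis is being pursued as introduction of the intervention occurs at the clinic level". No method is named there.

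Section 3.2.5 gives the primary outcome for these models, which "is defined as time to first missed pharmacy pick-up (> 7 days late"), and then the analysis: "we will use Kaplan-Meier estimates of time to the primary outcome, stratified by intervention condition, using log rank tests". This is the only place where a primary test for CAG and UAG is fixed. It mentions no clinic, matched pair, frailty term or robust variance.

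The same section plans the sample size on clustering. It takes "65% of patients are at least 7 days late for a pharmacy refill visit" in the first year, notes that "95% of clinics fall within 15% (that is 50 to 80) of this estimate", and concludes that "a conservative matched co-efficient of variation is estimated to be 0.10". The effect is also stated: "We assume a 50% reduction in missed pharmacy visits due to CAG and UAG". Appendix 6 tabulates power by number of matched clusters, patients per cluster and coefficient of variation. For the secondary outcomes of viral suppression and satisfaction, Section 3.2.5 names mixed effects models.

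**The concern.** A log-rank test assumes that patients' event times are independent. Here patients in one clinic share staff, stock-outs, opening hours and local practice, and the protocol itself expects clinics to differ. With five clinics per arm, the precision of the comparison is set largely by how much clinics vary, and the log-rank variance leaves that out.

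Both randomised primary comparisons are affected. P values would be too small, as would the standard error of any treatment effect derived from the same patient-level analysis. Section 1.1 says the study is to supply the data the Government needs to scale the models nationally, so a false positive would have consequences. The power figures in Appendix 6 also describe a different analysis from the one specified.

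**Working it through.** **Inputs.** From Section 3.2.5: event proportion p = 0.65, matched coefficient of variation k = 0.10, 120 patients per clinic and five clinics. Control clinics are assumed to match this in number and size; the protocol does not give a control-clinic enrolment figure. Follow-up is 12 months (Section 3.2.6).

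**1. The protocol's own power figure.** The standard matched-pair cluster formula with n pairs, j patients per cluster and two-sided alpha 0.05 is

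power = Φ( √[ (n−2)(π0−π1)² / { [π0(1−π0)+π1(1−π1)]/j + k²(π0²+π1²) } ] − 1.96 ).

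For π0 = 0.6, π1 = 0.3, k = 0.1, j = 30 and n = 5:

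- numerator 3 × 0.09 = 0.27
- denominator 0.45/30 + 0.01 × 0.45 = 0.0195
- √(0.27/0.0195) = 3.72, so power = Φ(1.76) = 0.961, against 0.96 in Appendix 6.

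The 15 distinct rows of Appendix 6 all reproduce within 2 percentage points. The stated power is therefore that of a matched cluster-level comparison. (A side point: 96% belongs to the row with 30 patients per cluster; the row with 120 shows 0.999.)

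**2. Type I error of the named test, analytically.** Ignoring clustering understates the variance by the design effect DE:

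- ICC = (k·p)² / [p(1−p)]
- DE = 1 + (120−1) × ICC
- actual type I error = 2 × [1 − Φ(1.96/√DE)]

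At p = 0.65 and k = 0.10: ICC = 0.065²/0.2275 = 0.0186, DE = 3.21, type I error = **27%**.

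Taking the stated clinic range of 50 to 80% with no gain from matching: SD = 0.15/1.96 = 0.0765, k = 0.118, ICC = 0.026, DE = 4.1, type I error = **33%**.

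**3. Simulation under no effect.** Five against five clinics of 120, exponential times, censoring at 12 months, normally distributed clinic proportions, 6,000 trials per setting:

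| Setting | Log-rank by arm | Log-rank stratified by pair | Paired t-test on clinic proportions |
|---|---|---|---|
| p = 0.65, k = 0.10 | 29.6% | 29.7% | 5.2% |
| p = 0.65, k = 0.118 | 34.8% | 35.0% | 5.0% |
| p = 0.65, k = 0.05 | 11.4% | 11.4% | 5.0% |
| p = 0.325, SD 0.075 | 34.2% | 34.5% | 5.2% |

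A separate run of 4,000 trials gave 29.9% and 34.5% for the log-rank at k = 0.10 and 0.118. A paired t-test on log clinic risks gave 5.5% and 5.2%. Stratifying the log-rank by pair does not cure the problem, because clinics still vary within pairs.

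**4. Sensitivity of the analytic figure (120 per clinic).**

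| p | k | Type I error |
|---|---|---|
| 0.65 | 0.05 | 12% |
| 0.65 | 0.20 | 53% (55% simulated) |
| 0.60 | 0.10 | 24% |
| 0.50 | 0.10 | 18% |
| 0.325 | 0.10 | 12% |

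**5. Power of a paired t-test on log clinic risks (five pairs of 120, simulated).**

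| Effect | k | Power |
|---|---|---|
| 0.65 to 0.325 | 0.10 | above 99% |
| 0.65 to 0.325 | 0.118 | above 99% |
| 0.65 to 0.325 | 0.20 | 92% |
| 0.65 to 0.325 | 0.30 | 66% |
| 0.8 to 0.6 | 0.10 | 81% |
| 0.65 to 0.4875 (25% relative reduction) | 0.10 | 75% |

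**The case against.** The best defence is that the protocol intends to respect clusters. Section 3.2.1 says so, the sample size is built on it, and mixed models are named for secondary outcomes. On that reading the log-rank sentence is merely silent on variance, clustered versions of the test exist, and an SAP could supply the detail. The intention is fair to acknowledge, and the defect is best described as a contradiction within the protocol. But Section 3.2.5 positively names a test, and as named it is the ordinary one. An SAP that follows it inherits the error; one that departs from it changes the stated primary analysis.

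Second, the 30% is conditional. The 65% refers to patients in their first year after starting ART, while participants must have been on ART for at least six months and are meant to be stable. Their event proportion and clinic spread may differ. This stands as a limit on the number, not on the direction: every setting examined with between-clinic variation is inflated.

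Third, equal control clinics of 120 are an inference from the matching, and Section 3.2.5 specifies no confidence interval for the comparison. Both points stand, and neither alters the conclusion about the test.

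Fourth, the paired test's power is above 99% only near the planning values and falls at the larger k values in Appendix 6 or with smaller effects. That is true, but it is the cost of five pairs. The ordinary log-rank only appears to avoid it by omitting the clinic variation.

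**Conclusion.** The concern holds. The primary CAG/UAG test as written does not fit the matched cluster design, contradicts the cluster-level analysis announced in Section 3.2.1, and is not the analysis that Appendix 6 powers. On the protocol's planning values the nominal 5% test has a type I error of 27% (analytic) to 30% (simulated), or 33 to 35% if matching gains nothing. These figures assume five clinics of 120 in each arm. Over k from 0.05 to 0.20 and event proportions from 0.325 to 0.65, the settings examined run from about 11% to 55%. This must be corrected, because it undermines the primary inference of both randomised comparisons.

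**What to change.** In Section 3.2.5, replace the log-rank as the primary test with a paired cluster-level analysis:

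- For each clinic, estimate the 12-month Kaplan-Meier risk (or log cumulative hazard) of a first missed pick-up.
- Take the within-pair difference of logs and test it with a paired t-test on 4 degrees of freedom, reporting the matching confidence interval.
- Keep the Kaplan-Meier curves by arm as display only.

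Other methods would be acceptable if their variance reflects between-clinic variation within pairs and is reliable with five pairs. Stratifying the log-rank by pair is not enough. A pair-permutation test is unsuitable as the primary test: five pairs give 2⁵ = 32 assignments, so its smallest two-sided p value is 2/32 = 0.0625.

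The cost is a wording change, with no extra sites, patients or data. Power stays above 99% for 65% against 32.5% at k of 0.10 to 0.118. The protocol should also state the lower power under less favourable assumptions, such as 92% at k = 0.20 and 66% at k = 0.30, and the planned number of patients per control clinic.
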